## Abstract

**Background::**

Severe acquired brain injury (SABI) rehabilitation should be as intensive and long as to allow the patients get the best independence and quality of life (QoL), but facing with the rehabilitation socioeconomic burden. Telerehabilitation (TR) could supply frail subjects requiring long-term rehabilitation.

**Methods::**

A multicenter, prospective, parallel design, single-blind trial will be conducted at the IRCCS Neurolesi Bonino Pulejo (Messina, Italy) and IRCCS Hospital San Camillo (Venice, Italy) involving patients suffering from SABI and requiring home motor and cognitive rehabilitation. We will investigate the use of TR, based on advanced Information and Communication Technology (ICT) solutions, taking into account that the supervision of rehabilitation at home will be enriched with the counseling and vital parameters monitoring. The enrolled patients will be balanced for pathology, and randomized in 2 groups, performing TR (G1) or standard rehabilitation training (G2), respectively, according to a pc-generated random assignment. TR will be delivered by means of an advanced video-conferencing system, whereas the patient will be provided with low-cost monitoring devices, able to collect data about his/her health status and QoL. In both the groups each treatment (either cognitive or motor, or both as per patient functional status) will last about 1 hour a day, 5 days/week, for 12 weeks. Two structured telephone interviews will be administered to the patients (when possible) and/or their caregivers, and to all the healthcare professionals involved in the patient management, 1 week after the beginning and at the end of the TR. All the patients will undergo a complete neurological and cognitive examination performed by skilled physicians and psychologists, blindly. Clinical evaluations will be administered blindly, before and after the treatments.

**Results::**

the data of this study should demonstrate that TR is at least non-inferior in comparison with the same amount of usual territorial rehabilitative physical treatments, taking into account patients’ functional recovery, psychological well-being, caregiver burden, and healthcare costs.

**Conclusion::**

data coming from this study could demonstrate the usefulness of TR in facing the rehabilitation socioeconomic burden of managing patients with SABI, so to allow the patients get the best independence and quality of life (QoL).

## Introduction

1

### Background and rationale

1.1

Severe acquired brain injury (SABI) is damage to the brain, occurring after birth from traumatic or nontraumatic causes, and often resulting in deterioration of physical, cognitive, and emotional functions.^[1]^ SABI include a variety of acute brain lesions characterized by the occurrence of variably prolonged coma (24 hours), and simultaneous motor, sensory, cognitive, and/or behavioral impairment that causes a certain degree of disability. Congenital, perinatal, or degenerative-progressive brain injuries are excluded from this definition. The most common causes of SABI are traumatic brain injury (TBI), anoxic encephalopathy and ischemic or hemorrhagic stroke. These conditions mostly affect individuals from the fifth decade onwards and represent about 40% of the SABI. Further nontraumatic SABI arises from brain tumors, infections, and toxic-metabolic encephalopathy.^[2]^ Despite the fact that steady progress has been made toward prolonging patients’ survival and several pharmacologic and neuromodulating strategies have been proposed, results on functional recovery of SABI are still scarce.^[1,2]^

Functional recovery following SABI usually reaches its peak at around 6 months, and begins to decline as soon as 1 year after SABI, although rehabilitation may be effective also in the chronic phase. Thus, the increasing use of rehabilitation postdischarge may result in better motor and cognitive recovery. To this end, supervised stroke rehabilitation in the community for up to 1 year was associated with faster recovery and better functional status than with unsupervised therapy.^[1,2]^

Unfortunately, due to healthcare costs, patients are discharged before reaching the desired autonomy.

Providing rehabilitation at home is limited by high costs and rehabilitation provider availability. Thus, the use of home-based, exercise-oriented interventions by means of TR may be decisive. Indeed, TR allows for continuity of service through the entire rehabilitation cycle including assessment, intervention, consultation, and education, and it has recently emerged as an effective tool to provide rehabilitation care to patients early discharged at home, increasing clinical outcomes, by affording early reintegration and positively enhancing QoL.

### Objectives

1.2

Aim of this project is to determine whether the use of TR in patients affected by SABI leads to greater (or at least equal) improvement in motor and cognitive function, functional communication, independence in self-care and domestic life, when compared with traditional in-home rehabilitation.

We also aimed to report on the presence of adverse events, feasibility and levels of user satisfaction of SABI patients (living at home) and their caregivers, which are associated to TR, monitoring of patient activities, and health status and telecounseling interventions.

Finally, we aim at evaluating the TR system-related cost-effectiveness, identifying the time necessary to amortize the initial investment for the Information and Communication Technology (ICT) equipment and services set up.

## Methods

2

### Trial design

2.1

This is a multicentric observational, rater-blinded, active-controlled, parallel-group pilot study to evaluate that TR is at least noninferior in comparison with the same amount of usual territorial rehabilitative physical treatments (UTRT). This study will be conducted at the Rehabilitative Units of IRCCS Centro Neurolesi, Messina (Unit 1) and of IRCCS Hospital San Camillo, Venice (Unit 2). Unit 3 (University of Messina) will help in Health Technology Assessment (HTA) evaluation and big data management. The study protocol was approved by the Ethical and Research Committee of IRCCS Centro Neurolesi “Bonino-Pulejo,” Messina, Italy (ID: 08/2018). The trial is registered under trial gov. (NCT03709875).

The study purpose will be explained to the participants, and patients’ consent will be obtained before the enrollment by the principle investigator.

The study has been funded by the Italian Ministry of Health: WFR: GR-2016-02361306.

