### Sample size

2.10

Based on the pilot samples during study, we calculated a minimal sample size of 60 participants per group in this study, given a power of >80% to detect an interaction in the 2-way repeated measures, an effect size of 0.61, 4 variables, and 2 repeated measurements.

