### Statistical analyses

2.11

The disability level will be the principal outcome, measured by WHODAS-12 (primary outcomes), and upper limp Fugl-Meyer (secondary outcome). The global cognitive status, assessed by MoCA, will be also a primary outcome. According to the data distribution, parametric or nonparametric statistical tests will be used. In particular, the independent Student *t* test or the Mann–Whitney *U* test will be used to compare the 2 groups, whereas the Student *t* test for unpaired samples or the Wilcoxon signed-rank test will be used to compare the data collected at the first evaluation and the end of the treatment (intragroup analysis). Linear correlation between variables will be computed by Pearson's coefficient or nonparametric Spearman's rank correlation coefficient. Statistical significance will be set at bilateral alpha level of 0.05. HTA assessment: Data will be collected by means of structured checklists, harmonized with all the units, to be administered to all involved actors. Any required data pooling, transformation, averaging, statistics and overall data processing will be performed by Unit 1 and 3 for assessing proper HTA indicators. With respect to cost analysis, specific direct, and indirect costs will be retrieved from each experimental study to allow performing Cost-Effectiveness and Cost-Minimization analysis within HTA3, to be possibly compared with corresponding cost analysis within HTA1. TR will be supported by the adoption of advanced ICT systems, necessary to set up videoconferencing between remote therapists and patient at home, monitor patient health status and activities, and store and process data collected during TR sessions. Monitoring systems will be composed by low-cost nonintrusive devices (such as bracelet or others).

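### The aim is non-inferiority, but the stated sample size and between-group tests address only a difference, so unless TR is significantly better the plan has no valid route to its claim

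*Protocol article*

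**What the plan says.** **Aim.** Section 2.1 (Trial design) gives the purpose as "to evaluate that TR is at least noninferior in comparison with the same amount of usual territorial rehabilitative physical treatments (UTRT". The Results part of the abstract says that "the data of this study should demonstrate that TR is at least non-inferior", and the Discussion repeats the expectation. Section 1.2 (Objectives) is broader: it asks whether TR "leads to greater (or at least equal) improvement in motor and cognitive function". Section 2.12 (Expected outcomes) uses similar wording. The aim is therefore mixed: non-inferiority throughout, with superiority as the more ambitious alternative.

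**Sample size.** Section 2.10 states: "we calculated a minimal sample size of 60 participants per group in this study, given a power of >80% to detect an interaction". The inputs are "an effect size of 0.61, 4 variables, and 2 repeated measurements".

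**Analysis.** Section 2.11 names WHODAS-12 and MoCA as primary outcomes. An independent t test or a Mann–Whitney "test will be used to compare the 2 groups", and "Statistical significance will be set at bilateral alpha level of 0.05".

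**Not stated.** The article gives no non-inferiority margin for either outcome and no rule for concluding non-inferiority. Sections 2.1 and 2.4 call the study a pilot.

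**The concern.** Non-inferiority needs evidence that any disadvantage of TR is smaller than a stated amount. A t test or Mann–Whitney test, as ordinarily used, starts from no difference and asks whether the data contradict it. Failing to contradict it does not limit how much worse TR might be.

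The direction of the possible error matters. Small numbers and noisy measurement make a non-significant result more likely. If such a result were taken as showing that TR is no worse, a weaker trial would be more likely to reach the favourable conclusion. The cost-minimisation analysis in section 2.11 also presupposes comparable effect, although the cost-effectiveness analysis planned beside it does not.

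**Working it through.** **1. Inputs**

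- Two-sided alpha 0.05: section 2.11.
- 60 per group, power above 80%, effect size 0.61: section 2.10.
- 40 per group: section 2.2 plans 20 stroke and 20 TBI patients per treatment, 20 + 20 = 40, read as the total over both units. The conflict with 60 is a separate matter, so both numbers are carried through.
- Margins, true deficits and a common SD: not in the article. All are assumed and expressed in SD units of the analysed measure.

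**2. The plan's own figure**

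The inputs of section 2.10 do not fix a unique number, because the article does not say whether 0.61 is a standardised mean difference or an ANOVA effect size, and gives no pre-post correlation. Read as a standardised difference d, with 80% power:

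n per group = 2(1.96 + 0.842)² / 0.61² = 42.2, so 43.

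With 60 per group, power = Φ(0.61/√(2/60) − 1.96) = 91.6%. That agrees with power above 80%, although 60 is not then the minimum. Exactly 60 arises if alpha is divided by 4 (normal approximation), or if a change score with correlation 0.3 is used; the article states neither. So 60 is not shown to be wrong. Every reading tried is a test of difference.

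**3. How often the planned test is non-significant when TR is truly worse**

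Approximately Φ(1.96 − d/√(2/n)). For d = 0.3 and n = 40: √(2/40) = 0.2236, 0.3/0.2236 = 1.342, Φ(0.618) = 0.73. The exact two-sample t results are:

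| Assumed true deficit of TR | 40 per group | 60 per group |
|---|---|---|
| 0.3 SD | 73.7% | 62.9% |
| 0.4 SD | 57.6% | 41.6% |
| 0.5 SD | 40.2% | 22.5% (22.47%) |

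**4. What a non-inferiority comparison could support**

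Assume a true difference of 0, one-sided 0.025 (equivalent to a two-sided 95% interval), 80% power and no baseline adjustment.

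Smallest margin = (1.96 + 0.842)√(2/n):
- n = 40: 2.802 × 0.2236 = 0.63 SD
- n = 60: 2.802 × 0.1826 = 0.51 SD

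95% interval half-width = 1.96√(2/n):
- n = 40: 0.44 SD
- n = 60: 0.36 SD

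n per group = 2(1.96 + 0.842)² / margin²:
- margin 0.5 SD: 63
- margin 0.4 SD: 99
- margin 0.3 SD: 175

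Conversely, power for margins of 0.3, 0.4 and 0.5 SD is 27%, 43% and 61% with 40 per group, and 38%, 59% and 78% with 60.

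**The case against.** Several objections are sound and limit the point.

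- **Misreading is not planned.** A reader might infer that the investigators will treat a non-significant result as non-inferiority. The article does not say so. Section 2.12 lists expectations and is not a decision rule. The misreading is a risk, not a stated plan.
- **The plan has one valid route.** It would be too strong to say that the named tests can never support the claim. A significant result favouring TR puts the whole 95% interval on the favourable side of zero, which excludes any margin.
- **Two-sided 0.05 is not an error.** It is the level behind the 95% interval recommended here.
- **A difference test fits part of the aim.** Sections 1.2 and 2.12 also hope for greater improvement, so the tests do not address the wrong question altogether. They leave the non-inferiority part without a rule.
- **A margin may be in a document not shown.** A missing margin alone would not be a finding in a condensed article. What stands is that the article does state its sample-size basis and its tests, and these do not match the stated aim. A margin given elsewhere would still leave section 2.10 sized for something else and section 2.11 with the wrong decision rule for that claim.
- **It is a pilot.** The label does not fit well with an abstract that speaks of demonstrating non-inferiority, or with a power claim above 80%. It does make restating the aim a reasonable alternative.

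**Conclusion.** The point holds as a mismatch between the stated aim and the stated sizing and analysis. If TR is not significantly better, the plan gives no valid basis for calling it non-inferior or at least equal.

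The risk is material. At 40 per group, a true deficit of 0.4 SD would go undetected more often than not (58%), and at 60 per group in about two cases in five (42%). These figures rest on assumed deficits, a common SD and an unadjusted t test, since the article gives no SD or margin. They show the order of magnitude and do not predict this trial's result. Because the main conclusion depends on it, the mismatch should be resolved before any unblinded look at the data.

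**What to change.** **Section 2.11.** Make the primary decision the TR minus UTRT difference in WHODAS-12 and in MoCA at the end of treatment, each with a two-sided 95% confidence interval. Claim non-inferiority only if the unfavourable limit excludes a margin in score points that is justified and fixed before any unblinded look. Test superiority after that. State that a non-significant difference is not evidence of non-inferiority.

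**Section 2.10.** Restate it as the margin or precision that the enrolled number supports. With 40 per group this is a margin of about 0.63 SD at 80% power with a true difference of 0, or a 95% interval half-width of about 0.44 SD, both unadjusted. Translate these into score points with a stated SD.

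**Alternative.** If so wide a margin is not clinically acceptable, restate the aim as superiority or pilot estimation and remove the non-inferiority claim from the abstract, section 2.1 and the Discussion.

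**Cost.** Wording changes and one clinical judgement on the margin. No extra patients are needed, but only because the plan then accepts either a wide margin or a weaker claim. A tighter margin at 80% power would need more: 63 to 175 per group for 0.5 to 0.3 SD.

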### Eligibility criteria

2.2

In both the clinical Units, we plan to enroll a total 40 stroke patients (20 for each treatment setting) and 40 TBI patients (20 for each condition) requiring home motor and cognitive rehabilitation.

Inclusion criteria are: age range 18 to 65 years; diagnosis of stroke and TBI (less than 1 year), according to neuroradiological and clinical assessments; availability of a home internet connection; the presence of a Montreal Cognitive assessment ≥16/30; the presence of a skilled caregiver.

### Exclusion criteria

2.3

Exclusion criteria will be: severe cognitive and behavioral impairments, cardiorespiratory instability or other medical illness potentially interfering with the treatment, severe limb spasticity, high-risk of spontaneous fracture, and substance abuse.

### Prescreening

2.4

Consecutive patients suffering from SABI, admitted to Rehabilitative Units of IRCCS Centro Neurolesi “Bonino-Pulejo,” Messina (Unit 1) and of IRCCS Hospital San Camillo, Venice (Unit 2), and requiring home motor and cognitive rehabilitation, will be evaluated for enrollment in this pilot study 2 weeks before the discharge to their homes.

### Randomization of participants

2.5

The enrolled patients will be balanced for pathology and randomized in 2 groups, performing TR (G1) or standard rehabilitation training (G2), respectively, according to a simple randomization scheme generated by a software (www.randomization.com).

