The training will be delivered by means of the Virtual Reality Rehabilitation System (VRRS). VRRS represents a real clinical and technological innovation that allows TR, integrating different rehabilitation modules (motor, cognitive, linguistic, and orthopedic). The system let a remote patient monitoring at home, thus reducing the costs of health care and the length of hospital stay. Such tool is conceived as a “central HUB” to which it is possible to connect, through a USB, a series of specific devices, that is, VRRS-Tablet. This latter is given to the patients to perform their exercises at home, under the control of a therapist by means of a hub-workstation, called Cockpit (Fig. 1). Patient's activity is controlled remotely from a workstation. The VRRS-Tablet contains different exercises, automatically adapted to the patient's performance, thanks to an optimal intensity training for every cognitive and/or motor condition. In fact, each exercise has a customizable setting efficiency. The VRRS-Tablet is equipped with patient and therapist mode: the former allows performing the exercises and monitoring the data produced, whilst the latter allows monitoring the patient's progress through the platform. These data will be stored in Cloud-based systems for further evaluation and statistical purposes (Unit 3). UTRT will be delivered in each patient's home, according to the local organizational system (i.e., Messina and Venice districts). The data coming from both clinical Units will be stored and analyzed at IRCCS for blind statistical analysis of primary outcome, and for HTA.

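### Simple randomisation does not deliver the balance by pathology, 20 per arm in each diagnosis, that the protocol states

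*Protocol article*

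**What the plan says.** Section 2.5 of the protocol article (Randomization of participants) makes two statements in one sentence. The first is the promise: "The enrolled patients will be balanced for pathology and randomized in 2 groups". The second is the method: "according to a simple randomization scheme generated by a software".

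Section 2.2 (Eligibility criteria) puts numbers on the balance. It plans "40 stroke patients (20 for each treatment setting) and 40 TBI patients (20 for each condition"), which is 80 patients, 40 per arm.

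The Methods paragraph of the abstract repeats the promise of balance and describes the allocation only as "according to a pc-generated random assignment". The article nowhere mentions strata, blocks, minimisation or separate lists by diagnosis.

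Section 2.11 (Statistical analyses) compares the two groups with an independent t test or a Mann–Whitney U test. Neither takes account of diagnosis.

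**The concern.** In simple randomisation each patient is allocated independently of all others and of any patient characteristic. It balances arm sizes and diagnoses only on average over many trials. A plan that states balance by pathology and fixes a number per arm per diagnosis needs a restricted scheme, and the one it names is unrestricted.

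What is at stake is control over a factor that the investigators themselves chose to balance, in a trial of 80 patients with two distinct diagnoses. As written, a chance difference in case mix is neither prevented by the allocation nor adjusted for in the stated comparison. A reader also cannot tell which was intended: the balance or the simple scheme.

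**Working it through.** **Inputs.** 40 patients per diagnosis and 20 per arm within each (section 2.2). Allocation probability 0.5, implied by the equal numbers. Simple randomisation (section 2.5). The 20-per-arm figure is a planning target with no formula behind it, so there is no calculation in the plan to reproduce.

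**Step 1: chance of meeting the target.** The number allocated to telerehabilitation within a diagnosis is Binomial(40, 0.5).
- One diagnosis exactly 20:20: C(40,20)/2^40 = 0.1254.
- Both diagnoses exactly 20:20: 0.1254² = 0.0157, or about 1.6%.

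**Step 2: chance of a visible imbalance.**
- A given diagnosis at 24:16 or worse: 2 × P(X ≥ 24) = 0.268.
- At least one of the two: 1 − (1 − 0.268)² = 0.464, or about 46%.
- For 25:15 or worse the same two figures are 0.154 and 0.284.

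**Step 3: what this does to case mix between arms.** The comparison is affected by the difference in stroke share between arms, not by each split alone. If both diagnoses split 24:16 in the same direction, both arms are still half stroke. If stroke splits 24:16 and TBI 20:20, the stroke shares are 24/44 = 54.5% and 16/36 = 44.4%, a gap of about 10 points. Summing the two independent binomials over all splits with a gap of at least 20 points gives a probability of 0.093, or about 9%.

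**Step 4: effect on the estimate.** The shift equals the gap in stroke share times the outcome difference between diagnoses. The documents give no such difference. If it is assumed to be 0.3 to 0.5 SD, a 20-point gap shifts the comparison by 0.20 × 0.3 = 0.06 to 0.20 × 0.5 = 0.10 SD. Section 2.10 plans on an effect size of 0.61.

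**Step 5: power.** Reading 0.61 as a standardised mean difference, with two-sided alpha 0.05, power is Φ(0.61 × √[n1·n2/(n1 + n2)] − 1.96).
- 40:40: Φ(0.61 × √20 − 1.96) = 77.9%.
- 44:36: Φ(0.61 × √19.8 − 1.96) = 77.5%.

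Unequal arms therefore cost about 0.4 points.

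**Step 6: other readings of the text.**
- Separate simple lists per diagnosis: each still gives 20:20 in only 12.5% of cases.
- One unstratified list fixed at 40:40: each diagnosis is 20:20 with hypergeometric probability 17.7%.
- Permuted blocks of 4 within each diagnosis: 40 patients fill 10 complete blocks, giving exactly 20:20.

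Section 2.10 gives a different total, 60 per group. That is a separate matter and does not rescue the scheme: with 60 per diagnosis (assumed), exact balance in both has probability 0.1026² = 1.1%.

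**The case against.** The best defence is that the word simple is used loosely. A computer-generated list for each diagnosis, holding 20 of each arm in random order, would satisfy sections 2.2 and 2.5 together. That is possible, but it is a restricted scheme and the article does not describe it. On this reading the sentence still has to change. It can also be said that 20 per arm is a plan, not an exact requirement, so 1.6% is a severe yardstick. That is fair, and the 46% and 9% figures are the better guide to practical size.

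Three stronger readings are tempting, and the documents do not support them.

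- *That the comparison is biased or confounded.* Simple randomisation is unbiased in expectation, and the error rate of the test already allows for chance imbalance. Steps 3 to 5 show a modest effect.
- *That 20:20 could be reached only by closing an arm or overriding the list, so that concealment fails.* A restricted list per diagnosis reaches 20:20 without either, and the article describes no forced balancing.
- *That leaving out centre is part of the same error.* The article promises no balance by centre, so nothing is contradicted. It does say that "UTRT will be delivered in each patient's home, according to the local organizational system (i.e., Messina and Venice districts"). However, section 2.6 links the regional settings to the feasibility and costs of telerehabilitation, not to WHODAS-12 or MoCA. Nothing shows centre to be a main source of outcome variation.

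It may also be said that covariate adjustment belongs in an analysis plan. In general it does, but here the article itself names unadjusted two-group tests.

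**Conclusion.** The point holds as a contradiction between the stated balance and the stated method. Under simple 1:1 randomisation with 40 patients per diagnosis, the planned split occurs in both diagnoses in about 1.6% of trials, and at least one diagnosis is 24:16 or worse in about 46%. The consequence is moderate: no bias in expectation, a negligible loss of power, and about a 9% chance of a gap of 20 points or more in stroke share that the stated tests would leave unadjusted. The probabilities rest on independent allocation at 0.5 and on recruitment of exactly 40 per diagnosis. The 0.06 to 0.10 SD shift rests on an assumed difference between diagnoses. The change should be made because it is cheap and the text needs correcting on any reading, not because the trial would be invalid without it.

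**What to change.** In section 2.5, replace simple randomisation with permuted-block randomisation stratified by pathology (stroke, TBI), with block lengths that add up to the planned number in each diagnosis. In section 2.11, include pathology as a covariate in the primary comparison, so that the analysis follows the allocation. If a restricted list per diagnosis was intended from the outset, describe it and drop the word simple.

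Stratifying by centre as well is optional. It is reasonable because the control treatment follows each district's local organisation. Its small downside is that incomplete blocks can leave a diagnosis slightly off target: with blocks of 4, each centre-by-pathology cell can differ by at most 2 patients, so a diagnosis is at worst 22:18.

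The cost is one new computer-generated list and two changes of wording, submitted as an amendment under section 4.2. No extra patients or visits are needed.
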